## Abstract

**Background:**

Decision aids (DAs) may be used to facilitate an autonomous, informed decision to cease smoking and promote the uptake of evidence-based cessation assistance (ie, behavioral support, nicotine replacement therapy, or prescription medication). However, knowledge is lacking regarding their effective elements and (cost-)effectiveness.

**Objective:**

We describe the development process of an online DA (called “VISOR”) that helps smokers to choose evidence-based cessation assistance. Additionally, we provide a description of the protocol of an ongoing randomized controlled trial in which the DA containing an explicit value clarification method (VCM) and tailored advice is compared with a DA without an explicit VCM and tailored advice.

**Methods:**

The development of “VISOR” was based on the International Patient Decision Aid Standards guidelines. Viewpoints of end users (collected through 20 interviews with smokers) and clinical and scientific experts (assessed using 2 Delphi studies with 24 scientists and 38 clinicians) were assessed regarding cessation tool decision making and preferred DA content. These findings, together with principles from the Self-Determination Theory, served as input for the development of the online DA. A first DA prototype was alpha-tested in September 2019 and beta-tested for usability in December 2019; feedback was incorporated and resulted in a final version. The final DA contains (1) an information section, (2) an optional knowledge quiz, (3) a brief smoking assessment, (4) intuitive decision, (5) intermediate advice, (6) an explicit VCM, (7) tailored advice, and (8) access information. A randomized controlled trial is currently being conducted to assess the DA’s (cost-)effectiveness compared to a DA that does not include the explicit VCM and the tailored advice; specifically, the DA’s effect on smoking abstinence, uptake of evidence-based cessation assistance, smoking abstinence mediated through uptake of evidence-based cessation assistance, and decisional conflict are investigated. Participants are randomly allocated to receive access to 1 of the 2 DAs and are asked to complete 5 questionnaires (including the baseline questionnaire) over a period of 12 months. To evaluate the effects of the DA on the outcome measures, logistic and linear regression analyses as well as mediation analyses will be carried out. An economic evaluation will be performed to assess the cost-effectiveness.

**Results:**

Data regarding the effect of the VISOR DA are currently being collected, and data collection is expected to be concluded in 2021.

**Conclusions:**

By making use of an iterative process that integrated different stakeholders’ perspectives (including end users), we were able to systematically design an evidence-based DA. The study will contribute to the current knowledge regarding smoking cessation DA application, the added value of explicit VCMs, and the effect of behavioral and informed decision-making outcomes.

**Trial Registration:**

Netherlands Trial Register NL8270; https://www.trialregister.nl/trial/8270

**International Registered Report Identifier (IRRID):**

DERR1-10.2196/21772

## Introduction

Smoking continues to kill, both on a global level [1] and in the Netherlands [2]. According to predictions, more than 8 million deaths per year will be caused worldwide by tobacco use by 2030 if evidence-based smoking cessation interventions are not put into use [3]. One way to reduce tobacco-related deaths is to promote the uptake of evidence-based cessation assistance, such as pharmacological support (eg, nicotine replacement therapy [NRT]) [4] and behavioral support (eg, counselling) [5]. Unlike non-evidence–based cessation assistance, such as acupuncture [6], evidence-based cessation assistance can greatly increase successful smoking cessation [7]. However, uptake of evidence-based cessation assistance is low in the Netherlands [8]. And, even if people are interested in using evidence-based cessation assistance, they still have to choose between the multitude of options that exist in order to make an informed decision. Making an informed decision requires people to gather and review information regarding cessation assistance options and weigh up all the advantages and disadvantages of those options [9]—tasks that can be difficult for unsupported lay people [10].

Decision aids (DAs) are interventions that are specifically designed to help users with those difficult decisional processes. DAs aim to facilitate informed decision making between different health or health care options by providing information and helping users to become aware of their own values ​​in relation to those options [9]. Often, DAs are used when people have to choose between different medical treatment options or if they are considering whether to participate in a screening program [9]. However, a systematic review regarding DAs for smoking cessation has also shown positive results in terms of increased quit attempts [11]. Insights from the Self-Determination Theory (SDT) also suggest that the offering of choice (as DAs explicitly do) enables individuals to engage in long-term behavior change, such as smoking cessation, by supporting their need for autonomy [12,13]. Nonetheless, only one DA for smoking cessation has previously been developed and tested in the Dutch setting [14]. And, while this DA was effective in promoting quit attempts and smoking abstinence, no effects were found regarding the use of cessation assistance [14]. As increased cessation assistance uptake could further improve cessation outcomes [7], we propose several limitations of the earlier DA that might need to be overcome to increase cessation assistance uptake and subsequent smoking cessation behavior. First, the earlier DA was paper-based and sent to people by mail, thereby limiting widespread dissemination. Offering a smoking cessation DA online could potentially reach many more people [15], especially given that the Dutch are likely to search for health-related information online nowadays [16]. Second, offering the DA online allows for a more flexible and interactive design that can be particularly interesting for people with a high need for autonomy [17]. And third, the aforementioned DA did not explicitly include methods that help users to become aware of their own values, even though explicitly including smokers’ values in their decisional process could potentially improve cessation assistance uptake rates [18,19].

So-called value clarification methods (VCMs, also referred to as value clarification exercises) can support users to “evaluate the desirability of options or attributes of options within a specific decision context, in order to identify which option he/she prefers” as defined by the International Patient Decision Aid Standards (IPDAS) [20]. The underlying belief is that users with clarified values (ie, users who know what is important to them) will be more likely to choose an option that reflects their own preferences, which is regarded as a prerequisite of high-quality decision making [9,20]. VCMs can either be explicit or implicit; the former refers to methods that involve the user actively engaging in an activity (eg, scoring certain statements), while the latter refers to the provision of information that is specifically linked to the decision at hand (similar to the aforementioned paper-based DA [14]), with the underlying belief that users will engage in cognitive processes themselves to reach a decision [21]. There is some evidence that shows that explicit VCMs are more effective than implicit VCMs (in terms of decisional processes) [22], especially in the long run [21] and when people are supported in understanding the implications of their clarified values for the decision [23,24]. One way to help users understand these implications is to show participants which options fit their clarified values [23] (ie, tailored advice following the VCMs based on the answers that were provided). Interestingly, the feasibility study of a digital DA for smoking cessation that did include an explicit VCM has shown promising results, both in terms of evidence-based cessation assistance uptake and smoking cessation outcomes [25]. Thus, explicit VCMs could potentially be used to enhance the effectiveness of DAs for smoking cessation. However, the feasibility study’s design (pretest and posttest assessment without a control group) limits the interpretability of the feasibility study’s findings [25], and it remains unclear whether such an explicit VCM results in significant changes in cessation rates and decisional outcomes.

Based on these limitations and the existing literature, an online DA, called “VISOR,” containing an explicit evidence-based VCM and tailored advice was developed that helps smokers to choose evidence-based cessation assistance tools. This DA was systematically developed and is currently being tested in a national randomized controlled trial (RCT) for its effect on individual decisional processes and smoking cessation attempts, as well as smoking abstinence compared to a DA without the explicit VCM component. Specifically, we aim to test the following hypotheses. 

H_1a/b/c_ is that a DA with an explicit VCM and tailored advice will lead to a statistically significant increase in smoking abstinence after 1 month (H_1a_), 6 months (H_1b_), and 12 months (H_1c_) compared to a DA without an explicit VCM and tailored advice: direct effect on smoking abstinence.

H_2a/b/c_ is that a DA with an explicit VCM and tailored advice will lead to a statistically significant increase in evidence-based cessation assistance use after 1 month (H_2a_), 6 months (H_2b_), and 12 months (H_2c_) compared to a DA without an explicit VCM and tailored advice.

H_3a/b_ is that the positive effect of a DA with an explicit VCM and tailored advice (vs a DA without an explicit VCM and tailored advice) on smoking abstinence after 6 months and 12 months will be at least partially mediated by the use of evidence-based cessation assistance at 1-month (H_3a_) and 6-month (H_3b_) follow-ups, respectively: indirect effect on smoking abstinence.

H_4_ is that a DA with an explicit VCM and tailored advice will lead to a statistically significant decrease in decisional conflict (state of uncertainty about which course of action to take) right after the DA compared to a DA without an explicit VCM and tailored advice.

In addition, it will also be tested whether the DA is more cost-effective compared to a DA without the explicit VCM component. This paper aims to thoroughly describe the DA “VISOR,” its development process, and the study protocol to test its (cost-)effectiveness.

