### Required Sample Size

The power calculation was based on the dichotomous outcome measure of smoking abstinence (primary outcome: 7-day point prevalence abstinence). The only previous RCT in the Netherlands testing the effect of a DA for smoking cessation on this outcome measure showed a significant effect (20.2% vs 13.6%) at 6 months [14]. To be able to significantly (α=.05; β=.20) detect the same effect in a 1-sided test, 398 smokers per arm are necessary at the end of the trial (796 in total). Considering 50% attrition over the intervention period, we aim to include 1592 smokers at baseline.

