### Trial Flow and Measurement Instruments

As participants register for the study via an online form, which includes their provision of informed consent and the creation of an account, participants are automatically randomized into 1 of the 2 groups (intervention or control group), allocating approximately 50% of respondents to either group. After this, they are asked to fill in the first part of the baseline questionnaire (t=0) consisting of 22-94 items (depending on the respective answers; eg, if the participants state that they have never attempted to cease smoking, no follow-up questions are posed), in which general demographic information (eg, age), smoking behavior, nicotine dependence, productivity loss, health care utilization, quality of life, and stages of decision making are assessed. Participants are excluded from the study if they indicate that they are <18 years old, do not smoke, are not motivated to stop smoking within 6 months, or only use e-cigarettes. Participants immediately receive access to 1 of the 2 DAs after being randomized, as this process is fully automated. After having accessed the DA, the second part of the baseline questionnaire is made available (t=1). The second part consists of 53-56 items regarding stages of decision making, the decision, the decision-making process, knowledge, perceived autonomy support, perceived competence, user evaluation, and recruitment channels.

One month after the baseline questionnaire (t=2), users are asked to fill in a short follow-up questionnaire consisting of 14-21 items regarding cessation assistance utilization, smoking cessation status, stages of decision making, and knowledge.

After 6 months (t=3) and 12 months (t=4), users are asked to fill in a longer follow-up questionnaire that consists of 16-88 items relating to cessation assistance utilization, smoking abstinence (7-day point prevalence abstinence and prolonged abstinence), and questions regarding smoking behavior for those that did not achieve smoking abstinence. Health care utilization, productivity losses, quality of life, and decisional regret are also assessed (again). During t=4, 2 qualitative items are included to assess users’ experience of having used the DA during their cessation attempt.

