#### Analysis of Primary and Secondary Outcomes

To assess the effects of the DA on dichotomous and continuous (primary and secondary) outcome measures, logistic and linear regression analyses will be conducted, respectively. Mediation analyses will be conducted to determine whether the effects of the DA on smoking abstinence are mediated through cessation assistance use. All analyses will include covariates that were selected a priori (as recommended by Gruijters [68] and De Boer et al [69]), if these are also associated with the 3 outcome measures as described in our hypotheses (ie, smoking abstinence, evidence-based cessation assistance use, and decisional conflict) within our sample. Demographic factors (ie, age, gender, and education) were selected for all 3 outcome measures. The Revised Fagerström Test for Nicotine Dependence was also selected for the smoking-related outcome measures, whereas stage of decision making was selected for decisional conflict. More information on the rationale for selecting those covariates can be found in Multimedia Appendix 1*.* Results will be reported from both the fully adjusted as well as crude analyses [68]. These analyses as well will be done with R [66], making use of the integrated development environment RStudio [67]. To test the robustness of the results, all analyses will be conducted according to 3 different approaches (if applicable): analyses based on (1) worst case scenario (dropout respondents are considered not to have changed), (2) multiple imputations, and (3) complete cases only. We will also test whether selective dropout has occurred in order to subsequently minimize the bias that this can cause.

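### Abstinence, the primary outcome, is tested at three unranked time points, while the sample size covers one 1-sided 5% test whose time point is left unclear

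*Protocol article*

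**What the plan says.** The first hypothesis in the Introduction of the protocol article has three parts: the intervention is expected to give a "statistically significant increase in smoking abstinence after 1 month (H_1a_), 6 months (H_1b_), and 12 months (H_1c"). The parts are not ranked. Table 3 lists 7-day point prevalence abstinence for hypothesis testing at each of the three follow-ups.

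Required Sample Size names this measure as the primary outcome without a time point. The planning rates come from an earlier Dutch trial that "showed a significant effect (20.2% vs 13.6%) at 6 months". The error rates are "α=.05; β=.20", and to detect that effect "in a 1-sided test, 398 smokers per arm are necessary at the end of the trial (796 in total"). It adds: "Considering 50% attrition over the intervention period, we aim to include 1592 smokers at baseline". By Trial Flow and Measurement Instruments, the last questionnaire is at 12 months. The rationale column of Table 1 speaks of one primary hypothesis, again without a time point.

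Under Analysis of Primary and Secondary Outcomes, to test robustness, "all analyses will be conducted according to 3 different approaches (if applicable"): worst case, multiple imputation and complete cases. None is called the main one. On the models: "Results will be reported from both the fully adjusted as well as crude analyses". Neither of these is put first. The article gives no rule for combining the three parts of the first hypothesis.

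**The concern.** The design pays for one test at 5%, but the primary outcome has three. The sample-size paragraph, where a reader would look for the deciding time point, points two ways: its effect is a 6-month effect, and its head count is needed at trial end, which is 12 months.

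The time points could well disagree. Under Potential Strengths, the authors themselves expect explicit value clarification to pay off in the long run and not necessarily early. If only one of the three tests is significant, the article gives no basis for saying whether the primary hypothesis was supported. The answer could then be settled after the results are known.

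Missing data add to this. With half the sample expected to be lost, counting dropouts as unchanged, imputing them and leaving them out can give different answers. The article does not say which one leads.

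**Working it through.** **Inputs from the article.** Rates 20.2% and 13.6%; 1-sided α = 0.05; power 0.80; 50% attrition; randomisation "allocating approximately 50% of respondents to either group"; three time points for the first hypothesis. **Assumed, because the article does not give it:** the correlation between the test statistics at different time points, taken from 0.3 to 0.9.

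**1. The plan's own figure.** Pooled-variance formula for two proportions, no continuity correction:

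n = [z₀.₉₅ √(2p̄(1−p̄)) + z₀.₈₀ √(p₁(1−p₁) + p₂(1−p₂))]² / (p₁−p₂)²

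With p̄ = (0.202 + 0.136)/2 = 0.169:

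- first term: 1.645 × √0.2809 = 0.872
- second term: 0.842 × √0.2787 = 0.444
- n = (0.872 + 0.444)² / 0.066² = 1.732 / 0.004356 ≈ 398 per arm
- total 2 × 398 = 796; with 50% attrition 796 / 0.5 = 1592

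All three stated figures reproduce exactly, for **one** 1-sided test at 5%. A 2-sided test would need 505 per arm.

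**2. Chance of at least one false positive over the three time points**, each tested 1-sided at 0.05, with no true effect. If the tests were independent: 1 − 0.95³ = 14.3%, an upper reference. For equally correlated statistics: 1 − P(all three z ≤ 1.645), from the trivariate normal distribution:

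| Assumed correlation | Any of three significant |
|---|---|
| 0.3 | 13.0% |
| 0.5 | 11.8% |
| 0.7 | 10.3% |
| 0.9 | 8.0% |

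**3. What the analysis variants add.** A simulation used 796 per arm, 13.6% abstinence in both arms, 50% dropout unrelated to outcome, assumed correlations of 0.3 to 0.9 in the underlying tendency to abstain, and 4000 replicates per setting.

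- One pre-named test: about 5%.
- Any of three time points (worst case, adjusted): 11% to 14%.
- Any of 12 analyses (three time points × worst case or complete cases × crude or adjusted; imputation left out): 15% to 20%.

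Most of the excess over 5% comes from the time points. The variants add about 4 to 5 percentage points.

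**4. Cost of keeping all three confirmatory with Bonferroni.** α per test = 0.05/3 = 0.0167, z = 2.128.

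- Power at 398 per arm: Φ[(0.066 × √398 − 2.128 × 0.530) / 0.528] = Φ(0.36) ≈ 64%.
- For 80% power: (2.128 × 0.530 + 0.444)² / 0.004356 ≈ 568 per arm, 1136 in total, 1136 / 0.5 = 2272 at baseline.

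**The case against.** The strongest reply is that the article never promises a 5% error rate across its hypotheses. The 5% appears only in the power calculation. The three parts are separately labelled and tied to their own time points. If each is reported as a claim about its own time point, each carries 5%. If all three had to succeed, error would not be inflated at all. This stands: the 8% to 13% applies only if any one significant result is allowed to carry the general claim. But the article does not exclude that use, and it ties its single powered test to no one time point.

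A second reply is that the lead missing-data approach and lead model are commonly fixed in an analysis plan, which is not shown here. That also stands in part. The three approaches are introduced as a robustness check, and the commitment to report crude and adjusted results makes hidden selection harder. A reader might multiply 3 × 3 × 2 to get 18 primary tests, and 1 − 0.95¹⁸ = 60%. The documents do not support that reading: the variants are highly correlated, and they are not set out as separate primary tests. The time point is different. The article addresses it itself and leaves it unclear.

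Third, sizing for retention at trial end is cautious for a 6-month test if losses only accumulate. That is fair, and the arithmetic is not in error. It still does not say which time point decides.

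Finally, abstinence is already called primary and decisional conflict secondary under Potential Strengths, so a hierarchy of outcomes partly exists. What is missing is a hierarchy of time points within the primary outcome.

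**Conclusion.** The point holds in a limited form. The primary outcome is attached to three unranked significance hypotheses, the sample size supports one, and the sample-size paragraph mixes a 6-month effect with a 12-month head count. If success may be claimed from any one time point, the chance of a false positive is about 8% to 13%, against the design's 5%. The correlations of 0.9 to 0.3 behind that range are assumptions.

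The absence of a lead missing-data approach and lead model is a smaller addition, and an analysis plan may already settle it.

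A reader might infer that the plan breaks a stated overall 5% guarantee, that the sample size is wrong, or that 6 months must be the deciding time point. None of these follows. No such guarantee is given, the figures reproduce exactly, and the text gives support to both 6 and 12 months.

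**What to change.** Record the following, dated, before anyone sees the outcome data:

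- Name one time point for the confirmatory test of 7-day point prevalence abstinence. Six months matches the powered effect; 12 months matches the requirement at trial end. The choice is the sponsor's, and Required Sample Size should be reworded to agree with it.
- Name one lead missing-data approach and one lead model (crude or adjusted). Label the others as sensitivity analyses.
- Make the other two time points secondary. If formal claims are wanted there, test in a fixed order or with Holm.

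This costs a few sentences. With one confirmatory test, 398 per arm, 796 in total and 1592 at baseline are unchanged. Keeping all three confirmatory with Bonferroni would mean accepting about 64% power at 398 per arm or recruiting 2272 at baseline. The downside of naming one is that the other two time points can no longer carry the primary claim alone.

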## Methods

An RCT is being conducted and will be reported in line with the CONSORT-EHEALTH checklist [26]. Participants are randomly allocated to receive access to either a DA with an explicit VCM and tailored advice (intervention group) or a DA without an explicit VCM and tailored advice (control group). Study materials (such as questionnaires, but not the DA) will be made available on the open science framework website, in line with recommendations in the field of behavioral science [27].

The study does not fall under the scope of the Medical Research Involving Human Subjects Act as indicated by the Medical Ethics Committee Zuyderland, the Netherlands (16-N-227). The development of “VISOR” and the accompanying studies are funded by the Dutch Cancer Society, UM2015-7744.

